#### Analyses of cost-effectiveness for those with co-morbid mood disorders

In a secondary economic analysis, we will estimate cost-effectiveness acceptability curves for improvement in the primary outcome measure (SF-36-PFS). We will use net benefit regression to assess whether there is an interaction between cost-effectiveness and the presence of anxiety or depression at baseline. We will quantify non-NHS costs and compare them between trial arms to judge whether they strengthen or weaken the interpretation of the primary economic evaluation.

Missing data from parental healthcare resource-use questionnaires from general practice records will be collected through data linkage, and will be used to check accuracy of reported healthcare resource use and to determine how many young people develop other illnesses.

### Safety

We will prospectively collect data on serious and non-serious adverse events reported to the clinician or research team during the intervention and follow-up period. These will be reported according to the sponsor’s guidelines. We will investigate whether young people randomised to one arm are at higher risk of having a serious deterioration in health compared to another arm. We will define a serious deterioration in health as: (1) clinician-reported serious deterioration in health, (2) a decrease of ≥ 20 in SF-36-PFS between baseline and 3, 6 or 12 months or scores of ‘much’ or ‘very much’ worse on the Clinical Global Impression Scale or (3) withdrawal from treatment because of feeling worse.

Safety outcomes will be analysed by the Data and Safety Monitoring Committee (DSMC) at 11 months after the start of recruitment, before the trial progresses from internal pilot to full trial and when approximately 50% of participants have been recruited (estimated 23 months after the start of recruitment).

Following the baseline mood assessment (using RCADS), the research team will not routinely monitor depression or anxiety. Participants will be made aware of this and if they are worried about anxiety or depression, or disclose information about this during the course of the trial, they will be advised to discuss this with their routine care providers (e.g. GP, paediatrician), and clinicians will inform them about relevant services if appropriate. Participants will be made aware that if they report any serious problem outside of business hours, it may not be followed-up until business hours resume and they should contact their GP, paediatrician or emergency service.

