### Randomisation

Participants will be randomised in a 1:1 ratio, by the research team, to receive either FITNET-NHS or Activity Management using an automated web randomisation service. Allocation will use minimisation to facilitate balance by age and gender, and preserve allocation concealment. Because of the nature of the intervention, it is not practical to blind either the participant, family or the clinical service to treatment allocation. GPs will be informed of the allocation.

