#### Duration of treatment period

Those allocated to FITNET-NHS will receive treatment for approximately 6 months but this will vary depending on how long it takes participants and their parents to complete the online chapters.

Participants allocated to Activity Management will receive treatment for 3 to 6 months. It will vary depending on the number of sessions (three to six) in the treatment course and the gap between follow-up sessions.

After completion of the treatment, patients will be discharged from the Bath specialist paediatric CFS/ME service to their local GP.

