As Activity Management and CBT are behavioural interventions it is not feasible to blind participants or clinicians to allocation. However, the research team have worked to ensure the information sheets present the two treatments in a balanced way, and recruiters have had training to try and encourage participant equipoise. The analyses will be conducted by a researcher blinded to treatment allocation. As we are investigating CFS/ME, the outcomes are patient-reported outcomes. These outcomes are consistent with illness domains that are the most important to patients. The outcomes at follow-up are not reported to clinicians to reduce performance bias.

There is potential for contamination between interventions because of contact between therapists of two treatment arms (working in the same treatment centre); however, both treatment arms are protocolised and adherence will be checked.

If differences in effectiveness are found between the treatments, further research will be required to explore mechanisms of effectiveness.

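### The between-arm serious deterioration comparison pools one equally scheduled component with two whose ascertainment depends on treatment contact and duration, which differ by design

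*Protocol article*

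**What the plan says.** The Safety section says the trial will examine "whether young people randomised to one arm are at higher risk of having a serious deterioration in health". Meeting any one of three components counts as an event:

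- Component 1: "We will define a serious deterioration in health as: (1) clinician-reported serious deterioration in health".
- Component 2: a fall of at least 20 on the SF-36-PFS from baseline to 3, 6 or 12 months, or one of the two worst ratings of change on the Clinical Global Impression Scale.
- Component 3: "withdrawal from treatment because of feeling worse".

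Component 2 comes from questionnaires sent at 3, 6 and 12 months in both arms (Outcome measures). Components 1 and 3 have no stated schedule. Adverse event data in general are those "adverse events reported to the clinician or research team during the intervention and follow-up period".

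Treatment contact is set differently by arm. FITNET-NHS uses email e-consultations roughly every 1 to 2 weeks for about 6 months, and "this will vary depending on how long it takes participants and their parents to complete the online chapters". Activity Management has three to six video appointments, and "Participants allocated to Activity Management will receive treatment for 3 to 6 months". The Randomisation section says that "it is not practical to blind either the participant, family or the clinical service to treatment allocation". Strengths and limitations adds: "The outcomes at follow-up are not reported to clinicians to reduce performance bias".

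**The concern.** A comparison of event risk is interpretable when both arms are observed alike. Component 2 meets that condition in timing. Component 1 does not, because a clinician can report only what reaches the clinician. Therapists know the allocation and do not see the follow-up questionnaires, so a report rests largely on contact with the participant. Component 3 can occur only while treatment is running, so a longer course gives it more time to occur.

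Pooled under an any-of-three rule, a difference in observation can look like a difference in risk, or can hide one. The monitoring committee analyses safety outcomes 11 months after the start of recruitment, before the pilot becomes the full trial, and again at about 50% recruitment. The trial will also report whether one arm carries more risk to participants aged 11 to 17.

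**Working it through.** The article gives no event rate, test or power for this composite, so there is no stated figure to reproduce. The check has two parts: how far the arms differ in observation, and what that could do to the pooled event under assumed rates.

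**Step 1. Contact and time in treatment** (taking 6 months as 26 weeks and 3 months as 13)

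- FITNET-NHS e-consultations: 26/2 = 13 to 26/1 = 26. This is derived; the article gives only approximate frequency and duration.
- Activity Management appointments: 3 to 6, as stated.
- Ratio of contacts: 13/6 = 2.2 to 26/3 = 8.7. Counting the three advisory calls to the local clinician: 13/9 = 1.4 to 26/6 = 4.3.
- Activity Management time as a fraction f of FITNET-NHS time: 13/26 = 0.50, midpoint 19.5/26 = 0.75, 26/26 = 1.00.
- The session and gap rules in the Activity Management section (2 to 5 follow-ups, 2 to 6 weeks apart) span 2 × 2 = 4 weeks to 5 × 6 = 30 weeks. Individual courses can therefore be shorter than 3 months or longer than 6.

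**Step 2. Effect on the composite at equal true risk**

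Assumptions, none of them from the article: component 2 occurs in q = 10% of each arm; a further r = 2%, 5% or 10% would be seen only through components 1 or 3; these events fall evenly over 26 weeks and are seen only during treatment. Then FITNET-NHS = q + r and Activity Management = q + f·r. For example, with f = 0.75 and r = 5%: 0.150/0.1375 = 1.09.

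| Case | r = 2% | r = 5% | r = 10% |
|---|---|---|---|
| f = 0.50 | 1.09 | 1.20 | 1.33 |
| f = 0.75 | 1.04 | 1.09 | 1.14 |
| f = 0.75, half of the later events still captured (f = 0.75 + 0.25 × 0.5 = 0.875) | 1.02 | 1.04 | 1.07 |
| f = 1.00 | 1.00 | 1.00 | 1.00 |
| f = 0.75, emails reveal half of what calls do: (q + 0.5r)/(q + 0.75r) | 0.96 | 0.91 | 0.86 |

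With 734/2 = 367 per arm, the f = 0.75 row means 367 × 0.005 = 1.8, 367 × 0.0125 = 4.6 and 367 × 0.025 = 9.2 extra events on FITNET-NHS. If a two-sided 5% test of two proportions were used (the section names none), it would reject in about 5.5%, 7.7% and 14.0% of trials.

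The base rate matters modestly. At f = 0.75, q = 5% gives 1.08, 1.14 and 1.20; q = 15% gives 1.03, 1.07 and 1.11.

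**Step 3. Component 3 alone**

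With a constant monthly withdrawal risk h, the chance of withdrawing over m months is 1 − (1 − h)^m. At an assumed h = 1%, this is 5.85% over 6 months, 4.42% over 4.5 and 2.97% over 3. The ratios are 1.32 and 1.97 from duration alone. That excess may be a real consequence of a longer treatment; it cannot be judged without weeks in treatment.

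**The case against.** The strongest reply is that the section only defines an event. It names no test and no leading safety contrast, and it does not rule out reporting by component, which is normally left to the analysis plan. That is a fair limit: the absence of a component split is not itself a fault. What remains is that the protocol fixes a pooled event for an arm comparison, and pooling is what mixes equal with unequal observation.

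Several further objections stand:

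- **Other routes exist.** Reports also reach the research team during follow-up. After Activity Management, a local review is requested within 6 to 8 weeks and up to three advisory calls are offered. Adding that review to the midpoint gives 19.5 + 6 = 25.5 to 19.5 + 8 = 27.5 weeks, close to FITNET-NHS. Local reporting back is not guaranteed, so the gap narrows but need not close.
- **Direction.** A reader might infer that FITNET-NHS will be made to look worse. The article does not support that. Emails may reveal less than calls of about 60 to 90 minutes, and some Activity Management courses may run longer.
- **Size.** A reader might take the contact ratio of 2.2 to 8.7 as the size of the bias. It enters none of the estimates in the table. Turning it into bias requires assuming that an email detects as much as a call and that no other route exists, and the article supports neither.
- **Withdrawals.** Both arms use the same three-level adherence rating, and stopping because of feeling worse may be true harm.
- **Relying on component 2 alone.** This would demote clinician-reported harm and miss questionnaire non-responders. It is also unblinded self-report. With baseline mean 49.8 and SD 24.8 (Sample size), (20 − 49.8)/24.8 = −1.20, so under a normal approximation about 11% start below 20 and cannot fall by 20; only the global rating can catch them.

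Finally, the stop criteria concern recruitment and acceptability, and no automatic action is tied to the composite.

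**Conclusion.** The point holds as a minor one. The pooled comparison combines one component observed on an equal schedule with two whose ascertainment depends on unblinded contact and time in treatment, and the two treatments differ in both. At equal true risk the pooled result may differ between arms.

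The direction is uncertain. The size is probably small to moderate: the ratios shown run from 0.86 to 1.33 and include 1.00, and they are 1.02 to 1.07 at the midpoint duration if half of the later Activity Management events are still captured. All of these rest on assumed event rates. The r = 10% column is demanding, since it needs as many participants to deteriorate only through components 1 or 3 as on the questionnaires.

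The documents do not support saying that the composite is invalid, that it is biased against FITNET-NHS, or that component 2 should replace it.

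**What to change.** Keep the full composite as the safety outcome, including for the monitoring committee, and prespecify the following:

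1. Each component is also compared separately by arm.
2. The component 2 comparison at 3, 6 and 12 months is shown beside the composite as the equal-schedule sensitivity analysis, with the number missing in each arm.
3. Components 1 and 3 are shown with the number of contacts and weeks in treatment by arm.
4. A composite difference driven only by components 1 or 3 is reported with the possible difference in ascertainment stated. It is neither dismissed nor read directly as a difference in risk.

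The cost is some wording and a little more analysis. Consultation numbers are already recorded for the economic evaluation, and both component 2 instruments are in the reduced questionnaire set sent to late responders. No extra participants, visits or questionnaires are needed. The limitation is that component 2 misses non-responders (the trial plans for 10% attrition) and is unblinded self-report, so it stays a check on the composite and not a substitute for it.

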## Discussion

Young people with CFS/ME should be offered referral to a specialist paediatric CFS/ME service [4]. However, most young people in the UK do not have access, or must travel very long distances to an NHS specialist service offering NICE-recommended treatments including Activity Management or CBT for CFS/ME. There is an evidence base for the using CBT to treat paediatric CFS/ME. However, none of the published paediatric trials have reported on cost-effectiveness. Although Internet-delivered CBT appears to be potentially useful, further evaluation is required before it is used within the NHS [44].

### Strengths and limitations

This will be the largest RCT conducted in paediatric CFS/ME. It is designed to investigate the effectiveness and cost-effectiveness of using FITNET-NHS, delivering online CBT, compared to Activity Management delivered via video calls, to treat paediatric CFS/ME in the UK. If effectiveness and cost-effectiveness are demonstrated for either arm, the NHS has the potential to deliver substantial health gains for the large number of young people suffering from CFS/ME but unable to access treatment because there is no local specialist service. If it is feasible this method could be used for other long-term conditions where young people do not have local specialist services. Results from the qualitative methods will tell us about patient experiences of the intervention content and mode of delivery, how to improve these types of interventions and how to deliver treatment from a single centre in the UK. Results will be disseminated as widely as possible including: open-access journals, conferences and public events. This is likely to benefit young people from other conditions, their families, clinicians and the NHS.

There is currently limited evidence of treatment effect in children with co-morbid mood disorders [45]. Most, but not all [46], studies in adults suggest that CBT is less effective in patients with co-morbid depression [47–49]. Anxiety and depression is common for young people with CFS/ME [8, 50, 51]. FITNET-NHS is designed to treat young people with co-morbid mood disorders as well as CFS/ME and this trial is powered to test whether the effects of FITNET-NHS differ in this subgroup of young people.

Our trial design includes usual care delivered by a specialist service. This is because it was felt to be unethical to offer no treatment to children in the control arm, though for many children in the UK ‘usual care’ is no treatment.

As Activity Management and CBT are behavioural interventions it is not feasible to blind participants or clinicians to allocation. However, the research team have worked to ensure the information sheets present the two treatments in a balanced way, and recruiters have had training to try and encourage participant equipoise. The analyses will be conducted by a researcher blinded to treatment allocation. As we are investigating CFS/ME, the outcomes are patient-reported outcomes. These outcomes are consistent with illness domains that are the most important to patients. The outcomes at follow-up are not reported to clinicians to reduce performance bias.

There is potential for contamination between interventions because of contact between therapists of two treatment arms (working in the same treatment centre); however, both treatment arms are protocolised and adherence will be checked.

If differences in effectiveness are found between the treatments, further research will be required to explore mechanisms of effectiveness.

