## Methods

The aims of this trial are to investigate whether Internet-delivered CBT, specifically designed for CFS/ME, (FITNET-NHS) is effective and cost-effective compared to a ‘usual care’ comparator of Activity Management (delivered via video call) for young people with CFS/ME who do not have access to a local specialist paediatric CFS/ME service. The trial is powered to explore effectiveness and cost-effectiveness in young people with mild to moderate co-morbid mood disorders.

This manuscript is in accordance with the Standard Protocol Items: Recommendations for Interventional Trials (SPIRIT) guidelines. See Additional file 1 for the Standard Protocol Items: Recommendations for Interventional Trials (SPIRIT) Checklist.

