### Sample size

Full trial: we plan to randomise 734 young people in the full trial. The study will proceed to full trial assuming the stop criteria (see below) are not met. Assuming 10% attrition (withdrawal or non-provision of primary outcome data) [16, 33], data on 660 young people will be available for the primary analysis. This gives 97% power at 1% significance to detect a 0.35-SD difference in treatment effect on the SF-36-PFS. The analysis of effectiveness in 198 young people with co-morbid mood disorders of anxiety and depression (30% of those recruited and with data available for analysis (after 10% attrition)) will have 80% power to detect a 0.4-SD difference at 5% significance. A difference of 10 points on the SF-36-PFS is considered to be the Minimal Clinically Important Difference (MCID) [36, 37]. The mean SF-36-PFS is 49.8 with SD 24.8 in young people with CFS/ME at assessment by the Bath specialist paediatric CFS/ME service (*n* = 1075). A 0.4-SD is 9.92 and, therefore, our trial is powered to detect the MCID of 10 in young people with co-morbid mood disorders of anxiety and depression.

We will perform sensitivity analyses on young people who fulfil the CDC diagnostic criteria. We estimate this will be 80% of those randomised (529 after 10% attrition) which will give us 98% power to detect a difference in treatment effect of 0.35 SD at 5% significance, which is at least the MCID.

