#### Analyses of effectiveness for those with co-morbid mood disorders

We will estimate the effectiveness of FITNET-NHS compared with Activity Management on the primary outcome in participant subgroups defined by the presence or absence of baseline anxiety or depression, by using the age- and gender-specific clinical thresholds for each subscale on the RCADS. Evidence that the intervention effect differs between subgroups will be examined by adding interaction terms to the multivariable linear regression model for the primary outcome only.

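### The Discussion claims power to test whether the effect differs in the mood-disorder subgroup, but the 80% calculated is for the effect within that subgroup; on the same basis the interaction test has about 65% for 0.4 SD

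*Protocol article*

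**What the plan says.** The Sample size section of the protocol article plans 734 randomised and 660 analysed after 10% attrition. It takes 30% of those analysed, 198 young people, to have co-morbid anxiety or depression, and says that the analysis of effectiveness in them "will have 80% power to detect a 0.4-SD difference at 5% significance". It then equates 0.4 SD (9.92 points at an SD of 24.8) with the 10-point MCID. This is a comparison of FITNET-NHS with Activity Management among young people who all have a mood disorder.

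The section on analyses for those with co-morbid mood disorders plans two things: effect estimates in each subgroup, and a test of whether they differ. For the second, "Evidence that the intervention effect differs between subgroups will be examined by adding interaction terms to the multivariable linear regression model".

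Strengths and limitations then says that "this trial is powered to test whether the effects of FITNET-NHS differ in this subgroup of young people". The article gives no power figure for the interaction.

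**The concern.** Power for an effect within a subgroup and power for a difference in effect between subgroups are separate quantities. The second carries the sampling error of both subgroups, so for a given size of difference its power is lower. The Discussion sentence attaches a power claim to the second question when only the first was calculated.

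What is at stake is how a null interaction is read. The same paragraph of the Discussion notes that most adult studies suggest CBT works less well with co-morbid depression, so a weaker effect in this subgroup is the possibility of interest. A reader who accepts the power claim could take a non-significant interaction as evidence that young people with anxiety or depression benefit equally. The data could not bear that weight unless the true difference in effects would have to be large to exist at all.

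**Working it through.** **Inputs.** From Sample size: "we plan to randomise 734 young people in the full trial"; 10% attrition, so 734 × 0.9 = 660.6 and "data on 660 young people will be available for the primary analysis"; subgroup 0.30 × 660 = 198; SD 24.8. The complement is 660 − 198 = 462. From Randomisation: "Participants will be randomised in a 1:1 ratio". Sidedness is not stated and is taken as two-sided. Normal approximation, in SD units.

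**1. Reproduce the stated figures.**
- Within the subgroup, 99 per arm: SE = √(4/198) = 0.142. Power = Φ(0.4/0.142 − 1.960) = Φ(0.854) = 80.4%, against 80% stated (80.0% with the noncentral t).
- Whole trial, 330 per arm, 0.35 SD, two-sided 1%: 97.3%, against 97% stated.
- CDC-criteria analysis, 529 in all, 0.35 SD, two-sided 5%: 98.1%, against 98% stated.

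So the article's calculations are two-sided and unadjusted, and the 80% is the within-subgroup comparison.

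**2. Interaction on the same basis.**

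SE = √(4/198 + 4/462) = √(0.02020 + 0.00866) = 0.170 SD, which is 4.2 points.

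Power = Φ(δ/0.170 − 1.960), where δ is the difference between the two subgroup effects:

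| δ (SD) | Points (δ × 24.8) | Power |
|---|---|---|
| 0.20 | 5.0 | 22% |
| 0.30 | 7.4 | 42% |
| 0.35 | 8.7 | 54% |
| 0.40 | 9.9 | 65% |

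Detectable with 80% power: (1.960 + 0.842) × 0.1699 = 0.476 SD; × 24.8 = 11.8 points.

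Analysed number for 80% power at 0.4 SD: (2.802² / 0.4²) × (4/0.3 + 4/0.7) ≈ 934.4, so 935 analysed and 935/0.9 ≈ 1,039 randomised, against 660 and 734.

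**3. Sensitivity for δ = 0.4 SD** (the varied values are assumptions).
- Subgroup prevalence with 660 analysed: 20% gives 54%, 40% gives 71%, 50% gives 73%. An even split is the most favourable, so no split reaches 80%.
- A one-sided 5% test would give 76%, but the other stated powers reproduce as two-sided.
- Baseline adjustment multiplies the SE by √(1 − r²), where r is the baseline-to-follow-up correlation:

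| r | Interaction power | Within-subgroup power |
|---|---|---|
| 0 | 65% | 80% |
| 0.3 | 69% | 84% |
| 0.5 | 78% | 90% |
| 0.6 | 84% | 94% |

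Interaction power of 80% at 0.4 SD requires √(1 − r²) = 0.4/0.476 = 0.840, so r of about 0.54. At r = 0.5 the difference detectable with 80% power is 0.476 × √0.75 = 0.412 SD, or 10.2 points.

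**The case against.** The strongest reply is that 65% is not the power of the test as planned. The interaction goes into a model that adjusts for baseline SF-36-PFS, age and gender, so 65% is an unadjusted figure; with a moderate correlation the 80%-power difference comes close to the MCID. The Discussion sentence also names no effect size or power level, so carrying 0.4 SD across to the interaction is the review's step. Both points stand, and they are why a range belongs beside the 65%. They do not support the sentence. The article gives no correlation, its stated powers take no credit for one, and any such credit raises the within-subgroup power as well, so the two figures remain different.

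A reader might infer several stronger things that the article does not support:

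- *That the test will probably miss a clinically relevant difference.* At about the 10-point MCID it is more likely to detect than to miss, even unadjusted. The 22% applies to 0.2 SD, about half the MCID, which the article nowhere calls clinically relevant.
- *That a headline aim fails.* The Abstract calls this a secondary subgroup analysis, and the claim about differing effects is made once, in the Discussion.
- *That the aims paragraph makes the same error.* It says "The trial is powered to explore effectiveness and cost-effectiveness in young people with mild to moderate co-morbid mood disorders". That is softer wording about effects in the subgroup, with no interaction claim. No calculation is shown for subgroup cost-effectiveness, but in a condensed article this is only a side remark.
- *That the clinical subgroup should give way to a continuous RCADS score.* That would answer a different question from the one for which the subgroup was sized, and is not needed to correct a power statement.

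**Conclusion.** The point holds as a mismatch between a claim and its calculation. The arithmetic under Sample size is right; the Discussion sentence assigns power to a question that was not calculated. On the article's own basis (198 against 462, unadjusted SD, two-sided 5%), interaction power is about 65% for 0.4 SD, and 80% is reached only at about 0.48 SD (11.8 points). With an assumed correlation of 0.3 to 0.6 the 65% becomes about 69% to 84%. The sample size, the primary analysis and the planned interaction test are unaffected. That a null interaction would be taken as equal effect is a risk the sentence creates; the article does not plan that reading.

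**What to change.** 1. In Strengths and limitations, replace the claim with one that matches Sample size: the trial has 80% power at 5% to detect a 0.4-SD effect of FITNET-NHS within the mood-disorder subgroup.
2. Beside it, give the interaction power or detectable difference with its assumptions: unadjusted and two-sided at 5%, about 65% for a 0.4-SD difference in effects, 22% for 0.2 SD, and 80% at about 0.48 SD. If credit for baseline adjustment is wanted, state the correlation assumed and its source.
3. State that the interaction is exploratory, to be reported as an estimate with its confidence interval, and that a non-significant result will not be read as equal effect.

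The aims paragraph and the RCADS-based subgroup definition need no change for this point. The cost is a few lines of text and a less favourable claim; no participants, data or analyses are added.
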